### Intervention periods and assessment time points

2.7

The intervention period will be 4 consecutive weeks, immediately following the conclusion of the training period. Then, patients and/or their guardians may choose to extend the intervention period for another 4 consecutive weeks until completing 8 weeks of TPNS. The 3 or 4 moments for assessment interviews will be the following: 1 week before the start of the intervention, immediately after the 4 weeks of intervention or immediately after the 4 and 8 weeks of intervention, and 4 weeks after the end of the intervention period, to identify any remaining effects of TPNS.

### Assessment interviews

2.8

In all assessment moments, patients and/or their guardians will participate in semi-structured interviews to determine the results of interventions regarding bowel movements and quality of life. The same member of the research team will be responsible for the interviews that will last approximately 40 minutes. The following surveys will be applied: a questionnaire addressing the current clinical status developed by our research group and previously used in another study that evaluated the impact of transcutaneous posterior tibial nerve stimulation in children and adolescents with FC^[31]^ (see questionnaire, Supplemental Digital Content 4); the modified Bristol Stool Form Scale for children (mBSFS-C)^[32–34]^ to analyze the stool consistency (see mBSFS-C, Supplemental Digital Content 5); the Bowel Function Score (BF-S)^[35]^ to evaluate the functional status of bowel habits (seeBF-S, Supplemental Digital Content 6); the Fecal Continence Index (FCI) questionnaire,^[36,37]^ based on the clinical evaluation of fecal continence (see FCI, Supplemental Digital Content 7); the Assessment of Quality of Life in Children and Adolescents with Fecal Incontinence (AQLCAFI)^[36,37]^ (see AQLCAFI, Supplemental Digital Content 8) and the Pediatric Quality of Life Inventory version 4.0 (PEDsQL 4.0)^[38,39]^ to assess the quality of life (see PEDsQL 4.0, Supplemental Digital Content 9). Lastly, a questionnaire addressing the evaluation of the applicability of the TPNS daily home sessions^[31]^ also developed and already used by our research group (see applicability questionnaire, Supplemental Digital Content 10).

In addition, patients will be monitored using a standardized week diary (stool frequency, stool consistency according to the mBSFS-c, frequency of fecal incontinence episodes, painful defecation, abdominal pain, excretion of blood in the stool, laxative use and their doses, and adverse effects such as pain, nausea, vomiting, diarrhea, and flatulence). The fulfilment of this diary will start seven days before each assessment moment. The doses of laxative medications will be registered, addressing any alterations as possible outcomes in the study's conclusion.

### Outcomes

2.9

Data analysis will focus on each assessment moment. The following clinical variables will be used for this analysis: the number of bowel movements per week, the number of fecal incontinence episodes per week, whether diapers or underwear protection is needed, whether defecation medications are needed, special diets, straining and pain while passing stool, presence of fecalomas, presence of abdominal pain, presence of bloody stools, need for enemas, and presence of perianal rashes or dermatitis. We will also analyze the results obtained by all the assessment instruments applied (mBSFS-C, BF-S, FCI questionnaire, AQLCAFI, and PEDsQL 4.0) to evaluate the outcomes of the functional status of bowel habits and the global quality of life.

As a secondary outcome, the applicability of TPNS will also be evaluated through the results of a specific questionnaire^[31]^ (see applicability questionnaire, Supplemental Digital Content 10), taking into account the practical difficulties and possible adverse events involved in using the method. All conditions that may be indirectly involved in the clinical results of TPNS, such as modifications in laxative doses or any clinical or dietary changes, will also be analyzed as secondary endpoints. Figure 2 summarizes the stages of the study and the Supplemental Digital Content 11 (SDC-11) features information about the Standard Protocol Items: Recommendations for Interventionist Tests (SPIRIT).

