### Statistical analysis

2.10

A descriptive analysis will be performed to characterize the patients before the beginning of the TPNS. A comparative statistical analysis will be conducted involving the results obtained for the variables analyzed at each evaluation time point. Continuous numerical data will be expressed as the mean ± standard deviation and median and Interquartile range (IQR). Proportions will be presented as percentages with their respective reliability intervals.

The comparison between the assessment time points will be performed using different statistical tests, according to the types of variables analyzed and to the normality distribution of data obtained by the results of the Shapiro-Wilk and Kolmogorov-Smirnov tests. Nominal variables will be analyzed using the McNemar test. Continuous numerical variables of parametric distribution will be analyzed using the *t*-test for paired samples. Continuous numerical variables of nonparametric distribution and ordinal variables will be analyzed using the Wilcoxon test. The significance level will be determined as 5% and will be analyzed using SPSS 22.0 software for Windows.

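### Abdominal pain is analysed only as present or absent, so a child whose pain lessens without disappearing counts as unchanged, although a diary started seven days before each visit also records it

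*Protocol article*

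**What the plan says.** All references are to the protocol article.

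- **Outcomes (2.9).** Two variables are counts: "the number of bowel movements per week, the number of fecal incontinence episodes per week". Later in the same sentence abdominal pain appears only as a presence item: "presence of fecalomas, presence of abdominal pain, presence of bloody stools".
- **Assessment interviews (2.8).** A week diary covers, among other things, "frequency of fecal incontinence episodes, painful defecation, abdominal pain, excretion of blood in the stool". On its timing: "The fulfilment of this diary will start seven days before each assessment moment". The same section also applies "a questionnaire addressing the current clinical status developed by our research group" at each interview. The questionnaire is in a supplement that is not shown.
- **Statistical analysis (2.10).** "Nominal variables will be analyzed using the McNemar test". For the other types: "Continuous numerical variables of nonparametric distribution and ordinal variables will be analyzed using the Wilcoxon test".

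Section 2.10 does not name abdominal pain, but a present/absent variable falls under its rule for nominal variables.

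**The concern.** McNemar's test uses only the children who change category. A child with pain at both visits is a concordant pair and drops out of the test, however much the pain has eased. The test can therefore respond only to complete disappearance or new appearance of pain.

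The Introduction names abdominal pain among the features commonly associated with constipation, and the Discussion says the study aims to demonstrate efficacy. With about 28 children there is little information to spare. A real reduction in pain could be reported as no significant change because the variable cannot show it. The same protocol asks about abdominal pain in a seven-day diary and already plans a test suited to a 0-7 count.

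**Working it through.** **1. The plan's own figure.** The only stated calculation is the sample size of 28 in 2.3, for a paired t-test on defecations per month: mean change 18, SD of changes 30, two-sided alpha 0.05, power 0.85.

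- Effect size: 18/30 = 0.6.
- Normal approximation: ((1.960 + 1.036)/0.6)² = 24.9, so 25.
- Exact noncentral t: n = 27 gives power 0.851, and n = 28 gives 0.864.

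The figure reproduces to within one patient. It rests on stool frequency, so the present point does not bear on it.

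**2. What McNemar needs.** With m discordant children all changing the same way, the exact two-sided p-value is 2 × 0.5^m. For m = 5 this is 0.0625, and for m = 6 it is 0.031. At least six children must lose their pain entirely, with none acquiring it, before the test reaches 5%.

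**3. Why a yes/no week saturates (conditional on an any-pain-in-seven-days rule).** For a child with daily pain probability p and independent days, P(any pain) = 1 − (1 − p)^7.

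| p | P(any pain in 7 days) |
|---|---|
| 0.5 | 0.992 |
| 0.3 | 0.918 |
| 0.2 | 0.790 |
| 0.1 | 0.522 |

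A fall from 0.5 to 0.3 barely moves the yes/no variable. A fall from 0.2 to 0.1 moves it clearly.

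**4. Size at n = 28.** The documents give no abdominal pain rates, so every pain input here is an assumption:

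- pain days are binomial(7, p) for each child;
- p varies between children as a beta distribution with concentration 2 to 4;
- the latent correlation between visits is 0.5;
- exact McNemar on any/none is compared with Wilcoxon signed-rank on days, both two-sided at 5%.

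| Mean share of days with pain | McNemar power | Wilcoxon power |
|---|---|---|
| 60% to 40% | about 6-18% | about 80-87% |
| 50% to 30% | about 26-34% | about 80-89% |
| 40% to 20% | about 55-59% | about 86-91% |
| 20% to 10% | about 37-41% | about 48-57% |

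The ranges span the two concentrations, and repeat runs differ by about 2 points. With no change, Wilcoxon rejects about 5% of the time, so its advantage is not bought with false positives. In the 50% to 30% case, the share of children with any pain falls only from 88-93% to 68-77%. In the three scenarios with a 20-point fall, 27-54% of children have fewer pain days but still some.

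**5. A different model.** Logit-normal variation was also tried (SD 1 between children, 0.7 between visits, probabilities for the median child). McNemar against Wilcoxon: 3% against 71% for 0.6 to 0.4; 11% against 76% for 0.5 to 0.3; 24% against 85% for 0.4 to 0.2. For a very large fall, 0.6 to 0.15, both do well: 84% against 100%. The direction does not depend on the choice of model.

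**The case against.** The strongest reply is that the article never says a seven-day record is being collapsed. A reader might infer that presence means any pain during the diary week and that the diary is filled in day by day. Neither is stated:

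- In 2.9 the words for a weekly count are attached to bowel movements and incontinence episodes, not to abdominal pain.
- Several items in the same list (diapers, special diets, fecalomas, enemas, perianal rashes) are not diary items in 2.8, so the list may come from the clinical-status questionnaire, whose recall window is not shown.
- The diary is described only as a week diary, and abdominal pain appears in it without the word frequency.

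This stands. The example of pain on most days falling to one day is conditional on the any-day reading. Nor can one assert that daily pain data are already being collected.

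Two further replies also stand in part. Presence of a symptom is a legitimate, readable outcome, and McNemar is the correct paired test for it; the weakness lies in the choice of variable, not in the test. The importance is also limited. The aims in the Discussion are bowel movements, stool consistency, incontinence and quality of life, and abdominal pain is one of about a dozen clinical variables alongside five instruments.

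What does not stand is that this is only detail left to a fuller document. Section 2.9 states the form of the variable explicitly, and a yes/no variable cannot register partial relief, whether it comes from the diary or from the questionnaire.

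**Conclusion.** The point holds as a worthwhile improvement to one outcome definition. The protocol fixes abdominal pain as present/absent without stating source or window, so lessening without disappearance cannot count.

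The loss in power depends on how frequent pain is. It is large (roughly 45 to 80 percentage points) if pain is present on about half of days or more at baseline, about 30 points for a fall from 40% to 20%, and only about 10 to 15 points for a fall from 20% to 10%. These figures rest on assumed pain rates, an any-pain-in-seven-days rule and daily recording; the documents supply none of the three.

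A reader might go further and conclude that the trial is too small or that its main result is compromised. The documents do not support that: the sample size is built on defecation frequency and reproduces.

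**What to change.** In 2.9, name the diary as the source for abdominal pain and define the outcome as the number of diary days with abdominal pain (0-7) in the week before each assessment. Compare visits with the Wilcoxon test already in 2.10. Keep present/absent, with its window stated, as a descriptive line.

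If the diary is filled in daily, the cost is one outcome definition, with no new instrument, visit or patient. If it holds a single weekly entry for pain, the count cannot be formed, and daily boxes would have to be added first. The Discussion describes the study as still in planning, with recruitment yet to begin, so that change could be made before the first child is enrolled. Daily boxes would add a little to the families' recording work.

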**Figure 2 F2:**
[figure not shown]
Flowchart of patients in the study.

### Statistical analysis

2.10

A descriptive analysis will be performed to characterize the patients before the beginning of the TPNS. A comparative statistical analysis will be conducted involving the results obtained for the variables analyzed at each evaluation time point. Continuous numerical data will be expressed as the mean ± standard deviation and median and Interquartile range (IQR). Proportions will be presented as percentages with their respective reliability intervals.

The comparison between the assessment time points will be performed using different statistical tests, according to the types of variables analyzed and to the normality distribution of data obtained by the results of the Shapiro-Wilk and Kolmogorov-Smirnov tests. Nominal variables will be analyzed using the McNemar test. Continuous numerical variables of parametric distribution will be analyzed using the *t*-test for paired samples. Continuous numerical variables of nonparametric distribution and ordinal variables will be analyzed using the Wilcoxon test. The significance level will be determined as 5% and will be analyzed using SPSS 22.0 software for Windows.

### Protocol amendments

2.11

REC will approve any modifications in the study before implementation. Data and source documents will be stored so that they can be accessed later by the REC. At the end of the study, the results will be submitted for publication in a peer-reviewed journal, following CONSORT compliance guidelines. Authorship of any related presentations or reports will be under the name of the collaborative group.

## Discussion

3

TPNS can be considered a promising, noninvasive, and safe method to be used as adjunctive therapy for treating constipation.^[18,27–30]^ However, there is a lack of published data that has investigated its use directed to treatment of children with FC.

This study's main objective was to assess the applicability and clinical outcomes of TPNS in children with FC. This study aims to demonstrate the efficacy of this promising method to increase the number of bowel movements and to improve stool consistency, to reduce the number of episodes of retentive fecal incontinence and to improve the overall quality of life indirectly.

Our research group has already developed a similar study to evaluate the applicability and clinical results of posterior tibial nerve stimulation in children with functional constipation.^[31]^ Thus, it will also be possible to compare the results obtained by these 2 minimally invasive neurostimulation methods in this clinical setting.

This study is currently in the planning phase, with the recruitment phase planned to begin in November 2020.

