### Study design and setting

2.1

This is a single-center, prospective, longitudinal, and interventional study designed to evaluate the applicability and clinical outcomes of TPNS in children with FC.

This research will be conducted at the Botucatu Medical School, Sao Paulo State University (UNESP), São Paulo, Brazil. The data collection period will be 18 months long, starting in November 2020. Patients will participate in daily sessions of TPNS for a period of 4 or 8 weeks. All patients will also be invited to participate in semi structured interviews at 3 or 4 moments: 1 week before the start of the intervention; immediately after the 4 weeks of intervention or immediately after the 4 and 8 weeks of intervention; and 4 weeks after the end of the intervention period. In these appointments, the aspects related to bowel habits and quality of life will be evaluated.

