### Patient selection and recruitment

2.3

The estimated sample size was 28 patients, calculated for a paired *t*-test (before and after intervention), based on an estimated mean increase of 18 defecations per month (according to data from a previous TPNS study 27), an estimated standard deviation of changes = 30, a 2-tailed α = 0.05 and a test power β= 0.85. The sample will include the Pediatric Gastroenterology Outpatient and Pediatric Surgery Outpatient Clinics of the Botucatu Medical School (UNESP). Patients will be invited to participate in an initial consultation to inform them about the research methods and apply eligibility criteria.

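### The Discussion promises to demonstrate efficacy, but one treated cohort with before-after tests can show only change over time, not an effect of TPNS

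*Protocol article*

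**What the plan says.** Section 2.1 (Study design and setting) frames the study modestly: "This is a single-center, prospective, longitudinal, and interventional study designed to evaluate the applicability and clinical outcomes of TPNS in children with FC". It describes a single treated group: "Patients will participate in daily sessions of TPNS for a period of 4 or 8 weeks". No control group, sham stimulation, randomisation or blinding is described anywhere in the article.

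Section 2.3 sizes the study for a paired before-after t-test: "The estimated sample size was 28 patients", from a mean increase of 18 defecations per month, an SD of changes of 30, two-sided alpha 0.05 and power 0.85. Section 2.10 plans only comparisons between assessment time points (paired t-test, Wilcoxon, McNemar).

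Section 2.5 asks families to keep to the treatment already prescribed, but allows changes that become necessary. Section 2.9 analyses such changes as secondary endpoints.

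The Discussion (section 3) first repeats the modest aim: "This study's main objective was to assess the applicability and clinical outcomes of TPNS in children with FC". The next sentence goes further: "This study aims to demonstrate the efficacy of this promising method to increase the number of bowel movements and to improve stool consistency". It extends the claim to incontinence episodes and quality of life. The following paragraph refers to the group's earlier tibial-nerve study: "Thus, it will also be possible to compare the results obtained by these 2 minimally invasive neurostimulation methods in this clinical setting". The Discussion states no limitation arising from the lack of a control.

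**The concern.** Efficacy is a causal claim: patients did better than they would have done without TPNS. Nothing in the design estimates what would have happened without it. A mean change from baseline combines any TPNS effect with natural course, regression to the mean, the attention of training and fortnightly supervised sessions, changes in laxatives or diet, and reporting by families who know that the child is being treated.

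The article itself gives reason to expect some of this. The Introduction says that most children with functional constipation respond to standard care, and the eligibility table (section 2.4) requires neither refractory disease nor a period of stable treatment.

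If the efficacy sentence stands, a significant paired test will naturally be reported as demonstrated efficacy in children. The 5% error rate would then be attached to a hypothesis that the test does not address. An unseen analysis plan could not repair this, because no analysis supplies a missing comparator.

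**Working it through.** **Inputs (section 2.3).** n = 28; mean change 18 defecations per month; SD of changes 30; two-sided alpha 0.05; power 0.85.

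**1. Reproduce the plan's figure.** Standardised change d = 18/30 = 0.60. The power of the paired t-test comes from the noncentral t distribution with n − 1 degrees of freedom and noncentrality d√n.
- n = 26: power 0.837
- n = 27: power 0.851, the smallest n that reaches 0.85
- n = 28: noncentrality 0.60 × √28 = 3.17, power 0.864

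The stated 28 is sound for its own purpose.

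**2. What the test rejects.** The null hypothesis is that the mean change is zero. The standard error is 30/√28 = 5.67 and the critical t on 27 degrees of freedom is 2.052. If the observed SD is 30, a mean change beyond 2.052 × 5.67 = 11.6 defecations per month is significant, whatever produced it.

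**3. Rejection probability when TPNS does nothing.** Let the non-specific change be x per month and the TPNS effect be zero. The noncentrality is x/5.67.

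| Assumed non-specific change x (per month) | x/30 | Noncentrality | P(p < 0.05) |
|---|---|---|---|
| 0 | 0 | 0 | 5.0% |
| 6 | 0.2 | 1.06 | 17.5% |
| 9 | 0.3 | 1.59 | 33.4% |
| 15 | 0.5 | 2.65 | 72.3% |

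The values of x are assumptions, because the protocol gives no figure for improvement without TPNS. Only the first row matches the nominal 5%, and it requires no drift at all.

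**4. Aim against design.** The aim in section 2.1, the first statement of the objective in section 3, the sample size in section 2.3 and the tests in section 2.10 all fit an estimate of within-patient change. The efficacy sentence in section 3 is the one that does not.

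**The case against.** The strongest reply is that the problem is one sentence in a Discussion. The same section gives the modest objective immediately beforehand, the sample-size, outcome and analysis sections are all framed as before-after, and an uncontrolled cohort is a legitimate choice for an applicability study where paediatric data are scarce. All of that stands, and it is why the remedy is confined to wording.

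Co-interventions are not ignored either. Treatment prescribed before entry was already in place at baseline. Changes must be reported to the team, laxative doses are recorded, and alterations are analysed (sections 2.5, 2.8, 2.9). There is also an assessment 4 weeks after treatment ends (section 2.7). These provisions help interpretation, but none shows what untreated children would have done over the same period.

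Four stronger readings are tempting and are not supported:
- *That a formal comparison with the tibial-nerve study is planned.* The article says only that "it will also be possible to compare the results obtained by these 2 minimally invasive neurostimulation methods". Sections 2.9 and 2.10 define no endpoint, test or ranking for it.
- *That the false-positive rate could be put at 86%.* This figure is the planned power at 18 per month. It becomes an error rate only if the whole expected change is non-specific, and nothing in the article says so.
- *That every outcome rests on a single baseline diary week.* The diary does begin seven days before each assessment, but section 2.8 also applies a clinical-status questionnaire and several bowel and quality-of-life instruments at every assessment.
- *That the sample size is wrong.* It reproduces.

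**Conclusion.** The concern holds for the efficacy sentence. With every patient treated and only within-patient tests planned, the study can estimate change during TPNS but cannot attribute it to TPNS. This follows from the design and rests on no assumed number.

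The size of the problem does rest on assumptions. Using the plan's n of 28 and SD of 30, with no TPNS effect and an assumed non-specific improvement of 6 to 15 defecations per month, the chance of a significant result is about 18% to 72%, against the nominal 5%. These figures illustrate the point and do not estimate the error in this study.

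The tibial-nerve remark is a lesser matter. A descriptive side-by-side is feasible. A conclusion that one method works better would not be supported, because the cohorts are separate and non-randomised.

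The correction is small but worth making, because the sentence sets what the study will be said to have shown.

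**What to change.** Replace the efficacy sentence in section 3 with: *to estimate the within-patient change in bowel movements, stool consistency, incontinence episodes and quality of life during TPNS added to ongoing treatment (mean change with 95% CI)*. Add one sentence stating that the uncontrolled design does not allow the change to be attributed to TPNS. For ordinal outcomes, which section 2.10 assigns to the Wilcoxon test, the matching estimate would be a median change with its interval.

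If results are set beside those of the tibial-nerve study, label the comparison descriptive: baseline characteristics and changes with confidence intervals for each cohort, with the reason given (separate, non-randomised groups).

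The design, sample size, data collection and tests stay as they are. The article describes the study as still in planning, so the change can be made before recruitment. The cost is a weaker headline conclusion.
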